#### Statistical analysis

Descriptive statistics (mean (standard deviation; SD) or median (IQ25–75)) will be used for continuous variables. Normality will be assessed using the Kolmogorov–Smirnov test. When the variables have a normal distribution, ANOVA and a post hoc Bonferroni test will be applied. If the variables do not have a normal distribution, a non-parametric test will be used to compare them. In this case, the Kruskal–Wallis test and Mann–Whitney test will be used to make post hoc comparisons.

A one-way repeated-measures ANOVA will be performed to analyze repeated measurements of continuous variables. Categorical variables will be presented as absolute frequencies and percentages and compared between groups using the Pearson chi-squared test or Fisher exact test. The odds ratio will be calculated with the 95% confidence interval for categorical postoperative outcome variables. The statistical analyses will be performed using SPSS version 21.0. Statistical significance is set at *p* < 0.05.

Before the digitization and statistical analyses, an investigator will review the data record form for completeness and correctness. At this time, missing data will be identified, drawn from source data, and filled into the case record forms if possible. We do not expect to obtain missing data with outcome variables because they are recorded in a mandatory manner in the electronic hospital files. However, missing pre- or intraoperative data will be treated with a regression imputation method. Data will be analyzed according to the intention-to-treat principle.

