### Data collection and management

A data collection notebook (CRD) will be compiled with all the variables described. Patients will arrive at the operating room with the first sheet completed (including demographic, analytical, respiratory function, and preoperative morbidity information). During surgery, intraoperative information will be collected on the subsequent pages. Before registration, the CRD pages corresponding to the patient’s stay in the PCU will be filled out. The CRD information will be completed before discharge. The CRD will include the patient’s in-hospital medical history and information that is not computerized. At the time of discharge, it will be kept in a locked cabinet in the anesthesiology department and will be completed with the data obtained during the day-30 visit. Data from the CRDs will be entered into the computer program SPSS, where they will be reviewed and accepted by an external clinical research organization (CRO). This CRO will ensure compliance with the study procedure and will control the possible errors that may occur.

The criteria for withdrawal from the study are as follows:
The protocol procedures cannot be followed for medical reasonsTransfusion of intraoperative blood productsDuration of OLV less than 60 minAdverse events related to any medication that is used during the study that prevents the continuation of the protocolThe patient voluntarily decides to leave the study or withdraws informed consentAny adverse clinical event that requires withdrawal from the study in the opinion of the researcherCompletion of the study

Patients who have to withdraw from the study because of these criteria will not be replaced by other patients. From the moment at which the withdrawal from the trial is decided, study samples of inflammatory markers will no longer be obtained. These patients will be followed by the members of the research team in the same way as patients who complete the study until hospital discharge, guaranteeing them the same healthcare. In these cases, only safety data (serious adverse events) will be collected for the study. For patients who withdraw their consent, no further patient data will be collected in association with the trial from the moment they inform the research team.

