### Power calculation

The primary outcome of this clinical trial is the comparison of the proportion of patients included in the different C–D classifications, which indicate the severity of postoperative complications for thoracic surgery. Two comparisons are planned: IV lidocaine + SS-PV vs remifentanyl IV+ SS-PV, and lidocaine PV + SS-IV vs remifentanyl IV+ SS-PV. The sample size is calculated based on the C–D classification ordinal scale. According to a similar study design by our research group, the standard deviation of this scale is approximately 1.5 units. Thus, it is necessary to include 48 patients per group with an alpha risk of 5% and a beta risk of 10% in a two-tailed comparison to detect differences ≥ 1 unit. Because losses are estimated to be 5%, the final sample size should be at least 153 patients (sample size calculator GRANMO version 7.12 April 2012).

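### The named between-group tests use none of the data collected before surgery, so some precision on Clavien-Dindo grade and 24-h PaO2/FiO2 is given up

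*Protocol article*

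**What the plan says.** The Statistical analysis section of the protocol article is specific about method. For normally distributed variables, "ANOVA and a post hoc Bonferroni test will be applied". Other continuous variables go to Kruskal-Wallis with Mann-Whitney comparisons. Categorical variables are "compared between groups using the Pearson chi-squared test or Fisher exact test", with odds ratios and 95% confidence intervals for categorical postoperative outcomes. Repeated measurements go to a one-way repeated-measures ANOVA. None of these is given a covariate, and no ANCOVA or regression model for a treatment contrast appears. The Randomization section describes a 1:1:1 list and names no stratification factor.

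Under Data collection and management, the first data sheet is complete when the patient reaches the operating room, "including demographic, analytical, respiratory function, and preoperative morbidity information". The Patients section makes lung-function testing part of eligibility. The visit table (Appendix 3) schedules a gasometry at visit 1, on day -1. PaO2/FiO2 is defined under Secondary outcomes as a single value at 24 h.

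The Power calculation section sizes the trial on the raw scale: "the standard deviation of this scale is approximately 1.5 units", with an "alpha risk of 5% and a beta risk of 10% in a two-tailed comparison to detect differences ≥ 1 unit".

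**The concern.** A baseline variable that predicts the outcome leaves explainable variation in the error term if the analysis ignores it. Putting it in the model removes that variation and takes account of whatever chance imbalance occurs. With about 51 patients per group and no stratification described, neither the design nor the named analysis makes use of the preoperative information. The plan even provides regression imputation for missing preoperative values, although no named test uses them.

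The clearest case is 24-h PaO2/FiO2, because a pre-treatment measurement of a closely related quantity is already scheduled. For Clavien-Dindo grade, age and lung function are reasonable candidates. The document does not itself call them prognostic.

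What is at stake is the width of the confidence intervals and a modest amount of power. The validity of the result is not in question.

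**Working it through.** **Inputs from the Power calculation section.** Difference 1 unit, SD 1.5, two-sided alpha 5%, power 90%, 48 per group, losses 5%, total 153.

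**Step 1: reproduce the plan's figure.** Unadjusted two-sample formula:

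n = 2 × (1.960 + 1.282)² × 1.5² / 1² = 2 × 10.51 × 2.25 = 47.3, rounded up to 48 per group.

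Losses: 48 / 0.95 = 50.5, rounded up to 51; 3 × 51 = 153. Both stated figures reproduce. Power at 48 per group is 90.4% by the normal approximation and 89.8% by the noncentral t. The SD of 1.5 enters with no reduction for covariates.

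**Step 2: the same design with baseline adjustment.** If the covariates explain a share R2 of the outcome variance, the residual SD is 1.5 × √(1 − R2) and the standard error of a two-group contrast is that SD × √(2/48). The document gives no R2, so 5-20% is an assumption. Power is for 1 unit at 48 per group by the noncentral t; the one or two degrees of freedom spent on covariates are ignored. The n for 90% power is 47.3 × (1 − R2), rounded up.

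| Assumed R2 | Residual SD | Standard error | Power | n per group for 90% |
|---|---|---|---|---|
| 0 (as planned) | 1.500 | 0.306 | 89.8% | 48 |
| 5% | 1.462 | 0.298 | 91.3% | 45 |
| 10% | 1.423 | 0.290 | 92.6% | 43 |
| 20% | 1.342 | 0.274 | 95.1% | 38 |

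The gain is therefore 1.5 to 5.3 percentage points over this range, and nothing if R2 is near zero.

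**Step 3: PaO2/FiO2 at 24 h.** The document gives no SD or correlation for this outcome, so only the ratio can be stated. ANCOVA on a pre-treatment value with correlation r multiplies the variance of the contrast by 1 − r²:

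- r = 0.3: 1 − 0.09 = 0.91
- r = 0.5: 1 − 0.25 = 0.75, worth 1/0.75 = 1.33 times the patients
- r = 0.6: 1 − 0.36 = 0.64

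These correlations are assumptions.

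**Step 4: which baseline gas value.** The Induction and monitoring section starts the study infusions when the paravertebral catheter is placed. The arterial sample labelled baseline in the Sample and measurement methods section is taken before one-lung ventilation, and so possibly after the infusions have begun. A covariate that treatment may already have affected should not be adjusted for. The day -1 gasometry is clearly pre-treatment.

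**The case against.** The case against is substantial, and much of it stands.

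- **The tests are valid.** Unadjusted comparisons are legitimate in a randomised trial, and this one has its stated power without adjustment. A reader might infer that the planned analysis is wrong or the trial underpowered for lack of covariates; Step 1 shows otherwise.
- **Chance imbalance is not bias.** A reader might infer that an imbalance in age or lung function would invalidate the contrast. Over repeated randomisations that variation is already counted in the standard error and the type I error. Adjustment improves precision; it does not repair a bias.
- **The size is assumed.** No R2 or correlation is given, and the lung-function entry criterion may narrow the range of FEV1 and weaken it as a covariate.
- **The power figures belong to a linear model.** A reader might take 91.3-95.1% as the power of the proposed proportional-odds analysis. It is not. In that model, adjustment moves the odds ratio away from the null and usually increases its standard error, so the gain arises differently. In simulations of an adjusted proportional-odds model under assumed prognostic strength, power rose from about 68% to 73% and from about 62% to 71%. That supports the direction only.
- **Baseline data may not be complete.** The plan itself foresees missing preoperative values, and the visit table does not say that the day -1 gasometry is arterial.
- **Repeated-measures ANOVA might be meant for the blood gases.** That is possible, but the outcome is defined as one value at 24 h, and that method is given no baseline covariate either.
- **An unseen analysis plan may name covariates.** It may. The point rests on the tests that this article itself names, which are a stated choice and not a gap.

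These arguments limit the claim to efficiency. They do not remove it.

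**Conclusion.** The point holds as a minor, optional improvement. The article names only unadjusted comparisons and describes no stratification, while usable pre-treatment data are collected anyway. On the protocol's own mean and SD approximation, the forgone power for 1 unit is 1.5 to 5.3 percentage points if baseline factors explain 5-20% of the variance. For 24-h PaO2/FiO2 the variance would fall by 25% if the correlation with the pre-treatment value is 0.5, and by 9% if it is 0.3. Both ranges are assumptions. The sample size is correctly computed, and the planned tests would give valid results as they stand.

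**What to change.** Make two changes to the Statistical analysis section, fixed before unblinding.

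1. Compare 24-h PaO2/FiO2 by ANCOVA with the day -1 value as covariate, not the sample taken before one-lung ventilation. Confirm first that the day -1 gasometry is arterial and that FiO2 is recorded with it.
2. For the two planned contrasts on Clavien-Dindo grade (each lidocaine group against remifentanil), pre-specify a proportional-odds model on the ordered grade with group, age and preoperative FEV1. Keep the unadjusted comparison as a sensitivity analysis. State in advance how sparse grades will be collapsed.

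Missing preoperative values are already provided for in the plan. Naming the covariates now also prevents their being chosen after an imbalance has been seen.

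The cost is a few sentences and a little more analysis work, with no extra patients or data; SPSS fits both models. The downsides are that the odds ratio becomes conditional on the covariates, and that the model adds a proportional-odds assumption, which is harder to check where grades are sparse.

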### Sample and measurement methods

BAL samples will be taken from the dependent lung 5 min before initiating OLV (BAS) and at the end of OLV (END) once TLV is established. Sampling will be performed using a 4.5-mm fiber-optic bronchoscope wedged into the selected segment of the bronchus of the left lower lobe and middle or right lower lobe with 100 mL of 0.9% saline solution in 25-mL aliquots to analyze inflammatory markers (interleukin (IL)-1, IL-2, IL-4, IL-6, IL-7, IL-8, IL-10, IL-12, tumor necrosis factor (TNF)-α, monocyte chemoattractant protein, and vascular endothelial growth factor). Arterial blood will be drawn to measure PaO_2_, SaO_2_, PaCO_2_, and the following inflammatory markers analyzed in BAL at four time points: baseline (before OLV), 30 min after initiation of OLV, the end of OLV, and 24 h after surgery. BAL and blood samples will be centrifuged, and the supernatant will be analyzed at a specialized laboratory. Biomarker concentrations will be analyzed using western blotting. The relationship between pro-inflammatory and anti-inflammatory markers is measured using the ratios of IL-6/IL-10 and TNF-α/IL-10.

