##### Secondary outcomes

Secondary objectives including the following will be the comparison between three groups of patients with the following laboratory or clinical data:

Secondary clinical outcomes
Postoperative pain intensity: Postoperative pain will be evaluated using the VAS at rest, during movement, and when coughing during the stay in the PACU and in the two days after. We will also record the doses of self-administered rescue analgesics by PCA pump during the first 48 h after surgery, as well as the cumulative morphine consumption in the first 48 h post-operation.Postoperative pulmonary complications (PPCs): PPCs will be classified using the definition applied in the ARISCAT study [21] (atelectasis, suspected pulmonary infection, respiratory failure, bronchospasm, aspiration pneumonitis, pleural effusion, and pneumothorax; Appendix 2). Because pneumothorax and pleural effusion are the usual outcomes after LRS in the nondependent lung, we will consider them to be complications only if they occur in the dependent lung. The time frame is up to 30 days after intervention.Postoperative cognitive dysfunction (POCD) is defined as the presence of a mini-mental test value less than 27 points at 3 days postoperative (in patients with a value of 30 points on preoperative mini-mental test) or if there is a drop of more than 3 points compared to the value obtained preoperatively (in patients with a mini-mental preoperative test value less than 30 points).The incidence of postoperative surgical complications, which is defined as the presence of any of the complications during the first 30 days postoperatively, as follows:

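### The only method named for repeated measurements has time as its sole factor, so it does not compare the three arms' biomarker and pain trajectories

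*Protocol article*

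**What the plan says.** In the protocol article, the section Statistical analysis gives repeated continuous measurements their own sentence: "A one-way repeated-measures ANOVA will be performed to analyze repeated measurements of continuous variables". No group or group-by-time term is named. For continuous variables in general, the same section says: "When the variables have a normal distribution, ANOVA and a post hoc Bonferroni test will be applied". Kruskal–Wallis with Mann–Whitney is the alternative for non-normal data.

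The section Secondary outcomes sets the purpose, which "will be the comparison between three groups of patients with the following laboratory or clinical data". The abstract likewise says that the inflammatory response will be compared between the three groups.

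The serial data are described under Sample and measurement methods. Blood gases and blood markers are taken "at four time points: baseline (before OLV), 30 min after initiation of OLV, the end of OLV, and 24 h after surgery". Lavage markers are taken twice, shortly before and at the end of one-lung ventilation. Pain is scored in the postoperative care unit and over the next two days.

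On missing data, Statistical analysis expects none in outcome variables, because these sit in the hospital's electronic files. It then adds that "missing pre- or intraoperative data will be treated with a regression imputation method". The section Data collection and management says that once a patient is withdrawn, "study samples of inflammatory markers will no longer be obtained".

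**The concern.** The mechanistic hypothesis in the Background is that lidocaine, by either route, attenuates the inflammatory response. That is a statement about differences between arms. The named test answers another question, namely whether the marker moves over time. Surgery and one-lung ventilation can be expected to move cytokines in every arm, so a significant result is likely whether or not lidocaine works. Running the test separately in each arm and comparing p-values would not compare the arms either.

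The missing-data wording adds a smaller difficulty. Biomarkers are secondary outcomes, but both lavage samples and three of the four blood samples are intraoperative. They could therefore fall under the sentence that expects no missing values or under the one that imputes them. If outcome values were filled in and analysed as observed, the between-arm standard error could be too small.

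**Working it through.** **1. The plan's own figure (Power calculation).** Inputs: SD 1.5, difference 1, two-sided alpha 5%, power 90%, losses 5%.

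n = 2 × (1.960 + 1.282)² × 1.5² / 1² = 47.28, rounded up to 48 per group. Then 48 / 0.95 = 50.5, rounded up to 51, and 3 × 51 = 153. Power at 48 per group is 90.4%. The figure reproduces and is not in dispute. It only sets the group size used below.

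**2. What each model tests, with 153 patients and 4 time points.**

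- One-way: value = mean + patient + time + error. The only F test is for time, on 3 and 152 × 3 = 456 degrees of freedom. A constant difference between arms is absorbed into the patient term, and a diverging one goes into the error.
- With a group factor: value = mean + group + patient + time + group-by-time + error. Group is tested on 2 and 150 degrees of freedom, and group-by-time on 6 and 150 × 3 = 450.

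**3. Simulated rejection rates at nominal 5%.** 3,000 runs, total SD 1. The within-patient correlation of 0.5 and the effect patterns are assumptions, because the document gives none. Simulation error near 5% is √(0.05 × 0.95 / 3000) = 0.4 percentage points.

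| Situation | One-way (time) | Group | Group-by-time |
|---|---|---|---|
| A. Arms identical; time means 0, 0.5, 0.8, 0.6 SD | 100% | 4.6% | 5.3% |
| B. Outer arms diverge to 1 SD apart; pooled mean flat | 4.1% | 95.0% | 99.8% |
| C. Constant 0.8 SD shift between outer arms; no time trend | 5.4% | 99.6% | 4.7% |

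The one-way test always rejects where there is nothing to find between arms, and stays at its nominal level where the arms truly differ. Row C also shows that an interaction p-value alone is not enough. Arm differences at stated times must be reported.

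**4. Missing biomarkers.** The document gives no missing rate for biomarkers, and its only loss figure is 5%. Suppose a missing end-of-ventilation value were filled once by regression on its baseline value and arm, then analysed as observed. Simulation: two arms of 51, missing completely at random, baseline-to-end correlation 0.3 to 0.7, with or without a random residual, 4,000 runs each.

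| Assumed missing | Estimated SE / true SE | Actual type I error |
|---|---|---|
| 5% | 0.94–1.00 | 5.0–6.5% |
| 10% | 0.91–0.96 | 5.8–7.7% |
| 20% | 0.79–0.90 | 7.8–11.7% |
| 30% | 0.74–0.84 | 10.0–14.6% |

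If arm is left out of the imputation model, the ratio is 0.98–1.03 and type I error 3.9–5.5%, so there is no material inflation. The cost is then in the estimate. Filled values carry no arm effect, so with balanced baselines a true difference δ becomes (1 − m) × δ + m × 0. At m = 20% that is 0.8 δ.

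**5. Timing of the baseline sample.** Induction and monitoring starts the paravertebral and intravenous study infusions at paravertebral catheter placement, after the patient is positioned. Sample and measurement methods says: "BAL samples will be taken from the dependent lung 5 min before initiating OLV (BAS) and at the end of OLV (END"). Baseline blood is drawn at some point before one-lung ventilation. Nothing places either sample ahead of the infusions, so the baseline may already carry a treatment effect.

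**The case against.** A reader might infer that the arms are never compared on these outcomes. The document does not support that. The ordinary ANOVA with Bonferroni, or Kruskal–Wallis with Mann–Whitney, can compare arms at any single time point, and the abstract assigns ANOVA to quantitative variables. Nor is every laboratory or pain outcome affected. The gas-exchange outcome is one value at 24 h, and cumulative 48-hour morphine is one value per patient. What remains is the serial biomarkers and serial pain scores.

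It can also be said that one-way was loosely meant as one between-group factor, and that full model terms belong in an analysis plan that is not shown. Both are possible. But the article does more than leave the terms open: it names a specific method for this class of data, and the name describes a model without a group factor. If something else was meant, the sentence still needs correcting.

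On imputation, a reader might infer that missing biomarkers will be singly imputed, with the standard error shrunk by the factor 1 − m for a missing fraction m. That would give a type I error of 7.8% at 10% missing and 11.7% at 20%. The text says neither single nor biomarkers, and by contrasting outcome variables with pre- and intraoperative data it can be read as limiting imputation to covariates. The factor 1 − m is also close to a worst case: 7.8% lies just above the simulated range at 10% missing, and 11.7% is the top of the range at 20%. The 24 h blood sample is postoperative and so outside the imputation sentence altogether.

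**Conclusion.** The main point stands as a mismatch between the named method and the stated aim. Followed as written, the repeated-measures test responds to the time trend and not to treatment, and no planned analysis compares the arms' trajectories. The rejection rates of 100% with identical arms and 4.1% with diverging arms depend on the assumed patterns and correlation. The absence of a group term does not.

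The missing-data point is secondary. The expectation of no missing outcomes does not fit the rule that stops biomarker sampling at withdrawal, for which intraoperative transfusion and one-lung ventilation under 60 minutes are among the criteria. Whether imputation would reach the biomarkers is unclear. If it did, once per value and with arm in the model, type I error would be about 5.0–6.5% at 5% missing and 7.8–11.7% at 20%, both assumed rates.

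Only secondary outcomes are involved. Neither the Clavien–Dindo comparison nor the sample size changes.

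**What to change.** Replace the repeated-measures sentence with a linear mixed model (or a mixed ANOVA) for each serial biomarker and pain score, with group, time and group-by-time as fixed effects and patient as a random effect. Use all observed values. Report each lidocaine arm against remifentanil, the two comparisons named under Power calculation, with 95% confidence intervals at stated times: for example, the end of one-lung ventilation and 24 h for blood markers, and the end of one-lung ventilation for lavage markers.

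Adjust for the baseline sample only if the sponsor confirms that it is drawn before the study infusions start. Otherwise adjustment, or reliance on change from baseline, could remove part of the treatment effect. In that case report unadjusted differences at each time.

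In the missing-data paragraph, acknowledge that biomarkers can be missing after withdrawal, restrict regression imputation to covariates, and state that biomarker outcomes are not filled in.

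The cost is a few sentences and slightly more analysis work. The planned software can fit the model, and no extra patients or samples are needed. The change should be made before the data are unblinded.

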**Methods/design:**

We will conduct a single-center randomized controlled trial involving 153 patients undergoing LRS through a thoracoscopic approach. The patients will be randomly assigned to one of the following study groups: intravenous lidocaine with more paravertebral thoracic (PVT) saline, PVT lidocaine with more intravenous saline, or intravenous remifentanil with more PVT saline. The primary outcome will be the comparison of the postoperative course through Clavien-Dindo classification. Furthermore, we will compare the perioperative pulmonary and systemic inflammatory response by monitoring biomarkers in the bronchoalveolar lavage fluid and blood, as well as postoperative analgesic consumption between the three groups of patients. We will use an ANOVA to compare quantitative variables and a chi-squared test to compare qualitative variables.

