#### Outcomes

##### Primary outcome

The primary outcome is the proportion of patients included in the different scales of the Clavien–Dindo (C–D) classification [20] in the three groups of patients. The greater the intensity of the treatment that is necessary to correct any postoperative complication, the higher the C–D classification will be considered. Any deviation from a normal postoperative course will be classified into grade I, II (minor complications), IIIa, IIIb, IVa, IVb, and V (major complications) of this classification (Appendix 1).

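### The primary outcome wording, the sample-size basis and the test rules for the Clavien–Dindo grade do not match, and the stated 90% power is not justified for the chi-squared rule

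*Protocol article*

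**What the plan says.** The Primary outcome section states: "The primary outcome is the proportion of patients included in the different scales of the Clavien–Dindo (C–D) classification". Deviations from a normal course are graded I, II, IIIa, IIIb, IVa, IVb or V, and a higher grade means that more intense treatment was needed.

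The Power calculation section repeats the outcome as a proportion, but then states: "The sample size is calculated based on the C–D classification ordinal scale". It adds that "the standard deviation of this scale is approximately 1.5 units" and asks for 48 per group to detect a difference of at least 1 unit (two-sided alpha 5%, beta 10%). Allowing for 5% losses, the total is 153. Two comparisons are planned, each lidocaine arm against remifentanil.

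The Statistical analysis section gives general rules by type of variable and does not mention the primary outcome by name:
- Continuous variables: "Normality will be assessed using the Kolmogorov–Smirnov test". If normal, ANOVA with Bonferroni post hoc tests; if not, Kruskal–Wallis followed by Mann–Whitney.
- Categorical variables: "Categorical variables will be presented as absolute frequencies and percentages and compared between groups using the Pearson chi-squared test or Fisher exact test". Odds ratios with 95% confidence intervals are added for categorical postoperative outcomes.

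The abstract carries the same split, with ANOVA for quantitative variables and "a chi-squared test to compare qualitative variables".

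**The concern.** Three parts of the plan treat the same outcome in different ways. The definition treats it as a set of proportions, the sample size treats it as a numeric score with a mean and SD, and the test rules can be read either way. A reader who follows the definition arrives at Pearson chi-squared or Fisher. A reader who follows the sample size arrives at a mean or rank comparison, and a Kolmogorov–Smirnov test on a coarse ordinal score then chooses between ANOVA and ranks.

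Two things are at stake. First, the choice of primary test could be made after the data are seen. Second, an unordered test discards the information for which the scale was chosen. The Discussion prefers Clavien–Dindo because other work pools complications of very different severity, yet the chi-squared p-value would not change if the labels for grade I and death were exchanged. The 90% power was not calculated for such a test.

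**Working it through.** **1. Reproduce the plan's figure.** Inputs from Power calculation: SD 1.5, difference 1, two-sided alpha 5%, power 90%.

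n per group = 2 × (1.960 + 1.282)² × 1.5² / 1² = 47.3, rounded up to 48.

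With 5% losses: 48 / 0.95 = 50.5, rounded up to 51; 3 × 51 = 153.

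Both figures reproduce exactly with the two-mean formula. Power at 48 per group is 90.4% (normal approximation) or 89.8% (t-test). The 90% therefore belongs to a mean comparison.

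**2. Why an unordered test differs.** The planning effect gives a non-centrality of 48/2 × (1/1.5)² = 10.67, which yields 90% on 1 degree of freedom. With no complication added as a level, the full scale has 8 levels, and a two-arm chi-squared has 8 − 1 = 7 degrees of freedom. The same 10.67 spread over 7 gives 65%. This only illustrates the mechanism, because the true chi-squared non-centrality depends on the whole grade distribution.

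**3. Power under assumed grade distributions.** The documents give no grade distribution, so these are assumptions. The reference arm is a discretised normal with SD 1.5; the mean difference is exactly 1 unit; there are 48 per arm; the test is pairwise at two-sided 5%. The scale has 8 levels, or 6 if the sub-grades are merged. Each scenario had 2,000 to 4,000 simulated trials, so the standard error is at most √(0.25/2000) = 1.1 percentage points.

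(a) Second arm obtained by a proportional-odds shift:

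| Levels | Means | Chi-squared | Mann–Whitney | t-test |
|---|---|---|---|---|
| 8 | 1.5 vs 0.5 | 88% | 98% | 96% |
| 8 | 2 vs 1 | 76% | 94% | 93% |
| 8 | 2.5 vs 1.5 | 68% | 92% | 91% |
| 8 | 3 vs 2 | 63% | 91% | 90% |
| 6 | 1.5 vs 0.5 | 88% | 98% | 97% |
| 6 | 2 vs 1 | 77% | 95% | 94% |
| 6 | 2.5 vs 1.5 | 71% | 91% | 91% |
| 6 | 3 vs 2 | 70% | 90% | 90% |

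(b) SD held at 1.5 in both arms (8 levels / 6 levels):

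| Means | Chi-squared | Mann–Whitney |
|---|---|---|
| 1.5 vs 0.5 | above 99% / above 99% | above 99% / above 99% |
| 2 vs 1 | 89% / 92% | 96% / 96% |
| 2.5 vs 1.5 | 73% / 73% | 92% / 90% |
| 3 vs 2 | 62% / 67% | 89% / 89% |

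In the last two rows of (b), chi-squared would need about 75 to 89 per arm for 90% power (non-central chi-squared approximation). In the first two rows it does well because the arms differ strongly in the share with no complication.

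**4. Result.** Mann–Whitney keeps 89% or more in every scenario, so the existing sample size suits it. Chi-squared runs from 62% to above 99%, depending on a distribution that the plan does not state.

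**The case against.** A reader might infer that the plan tests the primary outcome by chi-squared. The document does not say so. The chi-squared sentences are general rules for categorical or qualitative variables. The Power calculation section calls the scale ordinal, and Mann–Whitney, an adequate test, already appears in Statistical analysis. Assigning tests to endpoints is also partly work for the full protocol or the statistical analysis plan, neither of which is shown. This stands: the point is not that a test is missing, but that the definition, the sizing and the rules that are stated point in different directions.

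A reader might also infer that the trial will fall short of 90% power. The documents do not support this either. The shortfall arises only if chi-squared is used, and even then some distributions give 90% or more. The scale can also be grouped as none, minor and major, following the article's own split. In a further set of assumed distributions this gave 73% to 95%, against 56% to 89% for all 8 levels. Grouping recovers much of the loss, but the plan does not specify it. Fisher's exact test deals with sparse cells but not with lost ordering.

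Finally, it would be too strong to say that the analysis cannot show which arm did better. The planned percentages and odds ratios give some direction. The chi-squared p-value alone does not, and the plan does not say which split of the grades an odds ratio would use.

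**Conclusion.** The concern holds as a mismatch. The outcome is worded as proportions, the 48 per group is a mean comparison, and the rules leave chi-squared, ANOVA and rank tests all open for the primary outcome. The sample-size arithmetic is correct.

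The 90% is supported for a mean comparison and approximately for a rank comparison; it is not justified for an unordered chi-squared over all grades. Under a 1-unit proportional-odds shift the difference is about 63–88% against 90–98% for Mann–Whitney. These ranges rest on assumed grade distributions, on no complication counting as the lowest level, and on 8 or 6 levels. The loss for chi-squared is therefore likely but not established. The mismatch in the text does not depend on the simulation.

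**What to change.** In Primary outcome and Statistical analysis, name one order-respecting primary analysis of each patient's highest Clavien–Dindo grade, with no complication as the lowest level. It can be Mann–Whitney, or a proportional-odds model giving a common odds ratio with its 95% confidence interval. Apply it to each of the two planned comparisons against remifentanil. State that the chi-squared/Fisher rule and the Kolmogorov–Smirnov check do not apply to this outcome, and keep the grade-by-arm table as descriptive. Align the abstract. If chi-squared is really intended, the sample size needs its own justification from a stated grade distribution.

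The recommended change is to wording only, with no new data or patients, and should be settled before unblinding. Its one statistical cost is the proportional-odds assumption, if that model is chosen.
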